**Figure 3 f3:**
[figure not shown]
Longitudinal determination of the activation status of immune cells within the ImmunBio-KHT trial: The patients’ immune status was determined from peripheral blood via flow cytometry-based immunophenotyping. The expression of several activation markers was determined and the percentage of positive cells were calculated. Graph **(A)** shows the percentage of CD69 positive T Helper cells and **(B)** of T Killer cells, respectively. The expression of CD25 on basophils is depicted in **(C)**, the expression of HLA-DR on monocytes is shown in **(D)** and the percentage of HLA-DR positive T cells in shown in **(E)**. In **(F)** the HLA-DR expression on NK cells is depicted, while **(G, H)** show the percentage of PD1 positive T Killer and T Helper cells. The line in each graph shows the median percentage of positive cells. The Kruskal-Wallis test was applied on all data sets and the significance levels were calculated based on the change from the initial time point (01). (01: n=136, 02: n=56, 03: n=46, *p value of ≤0.5, **p<0.01, ***p<0.001,****p<0.0001).

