Postoperatively, a significant increase of eosinophilic and neutrophilic granulocytes (**Figures 2B, C**) and of monocytes (**Figure 2G**) has been detected in the peripheral blood. In addition, a significant increase in the percentage of monocytic myeloid-derived suppressor cells (MDSCs) and granulocytic MDSCs has been found (**Figures 2D, H**). The cells of the adaptive immune system, namely the B cells and T cells decreased in the periphery postoperatively (**Figures 2E, F**). A significant decrease in absolute cell counts has also been noticed for the dendritic cells (DCs) on day 7 after surgery (**Figure 2A**). The RCT however, caused a general decline of the immune cell counts in the periphery for all presented immune cell populations. A significant decline has been detected for the DCs (**Figure 2A**), the B cells (**Figure 2E**) and the T cells (**Figure 2F**). For the eosinophils (**Figure 2B**) and the neutrophils (**Figure 2C**), the cell counts generally decreased to the initial level that has been determined before therapy. Even though the cell counts of the monocytic MDSCs (**Figure 2D**) declined after RCT, they were still significantly higher than before surgery. For the granulocytic MDSCs on the other hand, the cell counts declined below the initial median cell count, even though this change was not statistically significant. In sum, a dynamic modulation of the different immune cell subsets has been detected during this therapeutic setting.

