The applied therapy had a significant effect not only on the cell counts, but also on the activation status of different immune cell populations (**Figure 3**). A significant upregulation of activation markers has mostly, but not exclusively been detected after RCT on several immune cell populations. On T Helper cells for instance, a significant increase in CD69 expression (**Figure 3A**), but also in PD1 (**Figure 3H**) expression has been detected. For the cytotoxic T cells, the same modulations in the activation state have been detected (**Figures 3B, G**). Furthermore, an increased CD25 expression has been found for the basophilic granulocytes (**Figure 3C**). Even though HLA-DR cannot be considered as a classical activation marker, it is included in our assay since a modulation of the expression of HLA-DR is commonly detected on immune cells. Since HLA-DR is a key molecule in antigen presentation, its differential expression might be relevant in tumor immunology. For T cells and NK cells, an increase in HLA-DR positive cells has been found after RCT (**Figures 3E, F**). On the other hand, HLA-DR positive monocytes were significantly reduced postoperatively but remained unchanged until after the RCT (**Figure 3D**).

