## Discussion

4

The here presented data of the peripheral immune modulation did already prove that the resective and reconstructive tumor surgery and subsequent RCT induces significant immune modulations and alters the frequency and activation of the immune cells that circulate through peripheral blood. More importantly, many of these modulated cell types and activation markers have already been found to be predictive in the context of cancer therapy. Neutrophils for example, have been proven to be prognostically relevant in numerous studies. However, it seems to be dependent on their functionality whether they are favorable for the outcome (5, 26). The HLA-DR expression on monocytes, which was found to be modulated after surgery and RCT in the ImmunBio-KHT patients, is known to be predictive for the response to ICIs in different cancer entities. More precisely, monocytes expressing high levels of HLA-DR predicted a favorable outcome in melanoma, lung cancer and HNSCC patients (5, 27). In line with that, mMDSCs which are characterized by a low expression of HLA-DR are currently investigated for their role in HNSCC in several studies. As MDSCs advance tumors through various mechanisms, their increase in peripheral blood after surgery is not favorable (28). The frequency of circulating cytotoxic T cells has been associated with the response to ICIs not only in HNSCCs, but also in other tumor entities. Particularly meaningful is the expression of activating or inhibiting molecules such as PD1 on these T cells (5, 29, 30). In line with that, we found significant modulations of the activation state of cytotoxic T cells and T Helper cells after RCT in the ImmunBio-KHT cohort. However, the interpretation of the increased expression of activation markers such as CD69 and PD1 on the T cells, is strongly depended on the patient cohort and the applied therapeutic interventions. The increase of PD1+ T cells for example, can be favorable in certain studies, but has also been found to be correlated with a worse prognosis in other trials (5, 29).

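### Section 3.2 says HLA-DR positive monocytes did not change between the postoperative and post-RCT samples, but the stated analysis tests only against baseline and does not support this

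*Protocol article*

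**What the plan says.** Section 3.2 describes the time course of HLA-DR on monocytes: "HLA-DR positive monocytes were significantly reduced postoperatively but remained unchanged until after the RCT". The first half compares 02 with 01, and the second half compares 03 with 02.

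The Figure 3 legend gives the method: "The Kruskal-Wallis test was applied on all data sets", and "the significance levels were calculated based on the change from the initial time point (01"). The Figure 2 legend says the same. The sample sizes and lowest significance level are printed as "01: n=136, 02: n=56, 03: n=46, *p value of ≤0.5". The line in each graph is the median.

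For eosinophils and neutrophils after RCT, section 3.2 says that "the cell counts generally decreased to the initial level that has been determined before therapy", which compares 03 with 01. For granulocytic MDSCs, the same paragraph says only that the fall below the initial median did not reach statistical significance.

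The Discussion (section 4) refers to "The HLA-DR expression on monocytes, which was found to be modulated after surgery and RCT" in the trial's patients. Section 2.7 gives the aim of this first analysis as depicting longitudinal change in the peripheral immune status and showing feasibility, with further interims after 500 and 800 patients.

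**The concern.** To say that a marker stayed the same between two time points, one needs an estimate of the change between them and some idea of its precision. Section 3.2 gives neither for 02 versus 03, and the legends do not list that comparison among those tested. If 02 and 03 both lie below 01, that does not show they are equal to each other: partial recovery and further decline during RCT would both fit.

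For patients who have surgery followed by RCT, 02 to 03 is the interval that isolates RCT. The Discussion singles out monocyte HLA-DR as predictive of response to checkpoint inhibitors. A reader could take from section 3.2 that RCT leaves this marker alone, although the stated analysis did not examine that question.

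**Working it through.** The document gives no power, margin, SD or interval for this comparison, so there is no figure of its own to reproduce. The check has two parts.

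**1. Which comparison was made, and on whom**

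- The claim concerns 03 versus 02. The stated significance covers 02 versus 01 and 03 versus 01 only.
- Kruskal-Wallis treats the three sets of samples as independent groups and does not use within-patient change.
- Section 3.2 says follow-up was incomplete and that some patients had RCT at another clinic.
- Section 2.1 gives two routes: surgery with adjuvant RCT, or definitive RCT. Table 2 lists 25 adjuvant, 20 definitive, 57 without RT and 48 not available (25 + 20 + 57 + 48 = 150). Operated patients without RT can supply an 02 sample but no 03 sample; patients on definitive RCT would be expected to do the reverse. The groups at 02 and 03 are therefore probably only partly the same patients. The number of pairs is not given.

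**2. How precise 02 versus 03 could be**

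Inputs: n = 136, 56 and 46 (Figure 3 legend). Assumptions made here: two-sided alpha 0.05 (the printed "p value of ≤0.5" read as 0.05), no multiplicity adjustment because none is stated, normal shifts, SD set to 1, independent samples, and a benchmark difference of 0.5 SD.

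Standard error: sqrt(1/n1 + 1/n2). Half-width: 1.96 × SE. Power: Φ(d/SE − 1.96).

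*02 versus 03 (56 and 46):*
- SE = sqrt(1/56 + 1/46) = 0.199
- 95% half-width = 1.96 × 0.199 = 0.39 SD
- Power at 0.5 SD = Φ(2.513 − 1.96) = Φ(0.553) = 0.71, so missed in 29% (30% with the t distribution, 31% with rank-test efficiency 0.955)
- Power at 0.3, 0.4 and 0.6 SD: 33%, 52% and 85%
- Simulated Dunn-type tests after Kruskal-Wallis at 136/56/46, unadjusted: missed in 32% to 38% at 0.5 SD, depending on where the third group lies

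An observed difference of exactly zero would thus be compatible with a true change of nearly 0.4 SD in either direction.

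*If the samples were paired*, SE = sqrt(2(1 − ρ)/pairs):

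| Pairs | ρ | 95% half-width (SD) | Power at 0.5 SD |
|---|---|---|---|
| 46 | 0.3 | 0.34 | 82% |
| 46 | 0.5 | 0.29 | 92% |
| 25 | 0.3 | 0.46 | 56% |
| 25 | 0.5 | 0.39 | 71% |

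The 46 is the most that the 03 sample allows. The 25 is the documented number of adjuvant RCT patients, used as an illustration.

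*01 versus 03, granulocytes (136 and 46):*
- SE = sqrt(1/136 + 1/46) = 0.171
- 95% half-width = 0.33 SD
- Power at 0.5 SD = Φ(2.931 − 1.96) = Φ(0.971) = 0.83; at 0.4 SD, 65%

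**The case against.** The strongest reply is that this is a descriptive interim in a trial that section 2.6 calls explorative. The Discussion does not repeat the *unchanged* statement and draws nothing from it, and no endpoint, sample size or design decision is shown to rest on it. That stands, and it limits the weight of the point. It does not supply the missing comparison, and depicting the time course is one of the two aims section 2.7 gives for this analysis.

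The miss rates can also be called hypothetical. The 0.5 SD is not in the document, the observations are repeated samples from one cohort, and with 46 pairs the power could exceed 80%. This is fair: the figures illustrate what the numbers could support and do not describe an analysis that was run. If 0.5 were really the significance threshold, power would be far higher (about 97% for 02 versus 03). Figures 2 and 3 are not shown, so intervals drawn there cannot be ruled out; the text and legends mention only a median line.

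Three stronger readings are tempting but not supported:

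- *Section 3.2 and the Discussion contradict each other on monocyte HLA-DR.* A marker that fell by 02 and was still low at 03 is modulated relative to 01 at both times, and also similar from 02 to 03. The wording is ambiguous but can be read consistently.
- *The granulocyte statement fails in the same way.* It is hedged with *generally*, has a stated test against 01, and has about 83% unadjusted power for 0.5 SD.
- *HLA-DR did in fact change during RCT.* Nothing in the document shows that either.

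**Conclusion.** The point holds for one statement. The claim that HLA-DR positive monocytes did not change from after surgery to after RCT is a 02-versus-03 claim, and the stated analysis covers only comparisons with 01, unpaired, on incomplete and probably only partly overlapping samples. With 56 and 46 independent samples, the half-width is about 0.39 SD and a 0.5-SD difference would be missed about 30% of the time. This rests on two-sided 0.05, normal shifts, no adjustment and the 0.5-SD benchmark chosen here. A paired analysis might do better or worse depending on the unreported number of pairs and their correlation.

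For granulocytes the point is minor: absence of a significant difference from 01 is worded as a return to the initial level, with no interval in the text (half-width about 0.33 SD). The point concerns reporting and the choice of contrast; it does not threaten the trial's design.

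**What to change.** 1. Estimate the 02-to-03 change in HLA-DR positive monocytes with a 95% confidence interval, from a paired analysis or a mixed model, and report the number of patients with both samples. A mixed model using all available samples is preferable, because complete pairs alone may be a selected group when some patients had RCT elsewhere.
2. Until that estimate exists, replace *remained unchanged* with a statement that the 02-to-03 difference was not tested, or that no difference was shown. Reserve *unchanged* for an interval lying within a margin that is stated.
3. Include the 02-to-03 contrast in the interims after 500 and 800 patients.
4. In the Discussion, say that the modulation after surgery and RCT is relative to time point 01, if that is meant.
5. For eosinophils and neutrophils, write that no significant difference from time point 01 was found, or give the interval. The granulocytic MDSC sentence already does the former.

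The cost is some rewording and one extra contrast on data already collected. The downside is a more cautious time-course statement.

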## Discussion

4

The here presented data of the peripheral immune modulation did already prove that the resective and reconstructive tumor surgery and subsequent RCT induces significant immune modulations and alters the frequency and activation of the immune cells that circulate through peripheral blood. More importantly, many of these modulated cell types and activation markers have already been found to be predictive in the context of cancer therapy. Neutrophils for example, have been proven to be prognostically relevant in numerous studies. However, it seems to be dependent on their functionality whether they are favorable for the outcome (5, 26). The HLA-DR expression on monocytes, which was found to be modulated after surgery and RCT in the ImmunBio-KHT patients, is known to be predictive for the response to ICIs in different cancer entities. More precisely, monocytes expressing high levels of HLA-DR predicted a favorable outcome in melanoma, lung cancer and HNSCC patients (5, 27). In line with that, mMDSCs which are characterized by a low expression of HLA-DR are currently investigated for their role in HNSCC in several studies. As MDSCs advance tumors through various mechanisms, their increase in peripheral blood after surgery is not favorable (28). The frequency of circulating cytotoxic T cells has been associated with the response to ICIs not only in HNSCCs, but also in other tumor entities. Particularly meaningful is the expression of activating or inhibiting molecules such as PD1 on these T cells (5, 29, 30). In line with that, we found significant modulations of the activation state of cytotoxic T cells and T Helper cells after RCT in the ImmunBio-KHT cohort. However, the interpretation of the increased expression of activation markers such as CD69 and PD1 on the T cells, is strongly depended on the patient cohort and the applied therapeutic interventions. The increase of PD1+ T cells for example, can be favorable in certain studies, but has also been found to be correlated with a worse prognosis in other trials (5, 29).

Surgery with subsequent RCT is the first-line therapeutic option for locally advanced HNSCC, whereas immunotherapy with ICIs is the first-line treatment in recurrent and/or metastatic HNSCC without curative surgical or radiotherapeutic options (15). Also, in (neo)adjuvant settings, ICIs are currently tested in clinical trials, as well as in different combinatory treatment regimens for HNSCC (4, 31). In the KEYNOTE-412 trial, examining the efficacy of additive pembrolizumab in locally advanced HNSCC patients undergoing definitive RCT, a statistically significant benefit in comparison to HNSCC patients without concomitant Pembrolizumab was almost achieved (32). RCT alone though, is also well-known to modulate the immune system (33), especially the local immune status of the tumor microenvironment. In particular, RT drives the upregulation of immune checkpoint molecules in the tumor microenvironment and alters the frequency of TILs in the tissue (16, 17, 34, 35). Though, it is not surprising that immune related markers for HNSCC have already been proven to be prognostically relevant during R(C)T alone (36–38). In addition, surgical interventions also influence local and systemic immune responses. In OSCC tumor tissue, a shift towards tumor-promoting M2-like macrophages was observed (39). In peripheral blood, among other parameters, a significant downregulation of CD45RO and an upregulation of IL-10 was observed on mRNA level in response to resective and reconstructive surgery (10, 11). Interestingly, the alteration of all analyzed biomarkers was highly dependent on the duration of surgery (10, 11). However, many of the aforementioned immune markers and modulations have not yet been tested in longitudinal settings. Thus, tremendous effort is put in the discovery of immunological biomarkers that are easily integrable into clinical routine and may be determined longitudinally throughout therapy (e.g. liquid biopsies), as many immunological markers change dynamically during therapeutic interventions (5, 17).

The ImmunBio-KHT trial was designed with wide-ranged inclusion criteria that allow the enrollment of a broad HNSCC patient collective that reflects the real-world situation. As HNSCC is a very heterogeneous tumor entity, this real-world patient cohort covers different tumor locations and monitors various confounding factors, such as the p16 status, the smoker’s history or the drinking behavior. With an intended patient number of 1000 in the intervention cohort, the ImmunBio-KHT trial offers the possibility to stratify the patients based on the aforementioned factors. Thereby, biomarkers for specific patient subgroups may be identified and immunological and clinical characteristics of responding and non-responding patients may be described. For HNSCC, numerous biomarker studies are currently running or planned. However, most trials are focusing on very specific treatment schemes or agents or on specific subpopulation of HNSCC patients, such as certain disease stages or particular tumor locations. Thus, the strength of the ImmunBio-KHT study is the fact that it will provide important information on the immune modulation and potential biomarkers during the early disease stages of patients undergoing surgery and/or RCT.

The design of the ImmunBioKHT trial includes a control cohort of patients that undergo surgery for functional diseases in the head-and-neck region without any known malignancy. This cohort fulfills the purpose to understand the changes that are induced by an extensive surgery in the head-and-neck region. Thereby, we aim to discriminate, whether the immunological changes from the pre-surgery to the post-surgery time point are only due to the surgery trauma or if there are effects that can only found in the tumor cohort and may thus be caused by the removal of the tumor and a subsequent change of the immunological milieu. However, we are aware that control cohort is not showing the same clinical features as the tumor patient cohort. Therefore, the control cohort cannot serve the function of determining baseline changes to understand what changes in the immune status of the patients are caused by the tumor itself and which immunological characteristics are due to the remaining clinical features of the individuals, such as the age or the smoking and drinking behavior. However, for this purpose, we can refer to a large data base of immunological data (immunophenotyping of the peripheral immune status) of normal healthy donors without any malignancy that show diverse clinical features and thus might be suitable for further comparative analyses.

Prospective clinical trials are needed for the purpose of biomarker identification and validation. Thus, the primary aim of the ImmunBio-KHT study is the definition of intra-tumoral and systemic immunological biomarkers in newly diagnosed and non-metastatic HNSCC. The ImmunBio-KHT trial will not only focus on the determination of immunological markers from the tumor tissue, but also on liquid biopsies from the peripheral blood. This design is advantageous, as immunological processes in the tumor tissue that may have a high informative and predictive value and can be associated with changes in peripheral immune parameters that are easier to obtain and measure. Thereby, predictive immune signatures from liquid biopsies may be developed, also by making use of Machine Learning-assisted approaches (40).

Apart from the direct measurement of immune cells (either in the tumor or the periphery), the design of the ImmunBio-KHT trial includes the sampling of the oral, tumor and bowel microbiome, as it is becoming ever more evident that the microbiome is not only impacting on the immune system but in consequence as well on immune-related tumoral processes. Different preclinical and clinical investigations have already proven that the microbial composition of the gut microbiome impacts on the response to ICIs in different cancer entities (20, 41–43). For HNSCC, however, only very few studies exist that have analyzed the microbiome of patients. Though, these studies found evidence that the oral microbiome might be involved in HNSCC tumorigenesis (14, 18–20). Based on that finding one can hypothesize that the microbiome might also have further predictive potential in advanced HNSCC. Thus, we aim to analyze the microbial composition in the ImmunBio-KHT trial in a prospective set-up along with the analysis of immunological markers from the tumor tissue and the periphery. These data sets will allow us to create a comprehensive picture of the interaction of the immune system and the microbiome. The interrelation and correlation of the systemic immune status, the local immune status of the tumor microenvironment and the composition of the microbiome has never been analyzed in depth in a large HNSCC cohort. Even without the aim of bridging these data to the patient outcome, the analysis of the microbiome along with the immune status will generate new insights on the immunobiology of HNSCC.

In this first interim analysis of the ImmunBioKHT trial, only the longitudinal data on the peripheral immune status of the first 150 patients of the intervention cohort is presented. Even though predictive and prognostic signatures cannot be built without associating the biological/immunological data with the clinical and oncologic characteristics of the patient cohort, this presentation of the first results proves the feasibility of this large observational trial. In the further course of this trial, the here presented data of the systemic immune status not only needs to be connected to the clinical data, but also to be brought into connection with the local immune status from the tumor tissue. Thereby, we aim to investigate whether the systemic immune status is able to reflect the immunological composition of the tumor micromilieu. The further plans also include the detailed analysis of the patients’ microbiome from stool, saliva and from the tumor tissue as predictive factors for HNSCC. Finally, we plan to connect the biological data sets with the confounding factors and the patients’ outcome.

